## 4.6 Data management and protection

All paper data containing identifying information (e.g. signed consent forms) and those that do not contain identifying information (e.g. filled adherence questionnaires) will be held securely in locked filing cabinets at the MSF office in Irbid. Electronic data will be password protected, and held on password-protected computers with only identified team members given access to the data and password. The encoded cohort dataset will have the coding removed after final analysis for this evaluation is completed. All data (other than active service data) will be stored for ten years following completions of the project and will then be permanently deleted and destroyed. Responsibility for this rests with the principle investigator.

## 4.7 Confidentiality

All cohort data extracted from the programme database for analysis, survey data and qualitative data will be treated confidentiality with no names recorded in datasets. The semi-structured interviews will be conducted in a private space. The focus group discussions content will be treated as confidential and all participants will be requested to agree and adhere to the confidential nature of the discussions.

## 4.8 Independent review

This study protocol will be submitted to the Ethics Review Board instituted by MSF. Written authorisations to implement the study will also be obtained from the Ministry of Health in Irbid.

# 5. Study implementation

## 5.1 Collaborative partnership

This will be a collaborative partnership between MSF-OCA, the Jordanian Ministry of Health and the London School of Hygiene and Tropical Medicine.

## 5.2 Timeline

The proposed timeline is shown below. Month 1 is February 2017.

**Table 3.** Proposed timeline for MSF OCA Irbid NCD Programme Evaluation 2017

|  |  | | Month 2017-2018 | | | | | | | | | | | | |
| --- | --- | --- | --- | --- | --- | --- | --- | --- | --- | --- | --- | --- | --- | --- | --- |
|  | 1  F | 2  M | | 3 A | 4 M | 5  J | 6  J | 7  A | 8  S | 9  O | 10  N | 11  D | 12  J | 13  F |  |
| Finalise protocol |  |  | |  |  |  |  |  |  |  |  |  |  |  |  |
| Ethics approval |  |  | |  |  |  |  |  |  |  |  |  |  |  |  |
| Implementation |  |  | |  |  |  |  |  |  |  |  |  |  |  |  |
| Cohort routine data collection |  |  | |  |  |  |  |  |  |  |  |  |  |  |  |
| Adherence Survey |  |  | |  |  |  |  |  |  |  |  |  |  |  |  |
| Qualitative research |  |  | |  |  |  |  |  |  |  |  |  |  |  |  |
| Clinical audit |  |  | |  |  |  |  |  |  |  |  |  |  |  |  |
| Cost data collection |  |  | |  |  |  |  |  |  |  |  |  |  |  |  |
| Cross-sectional survey secondary analysis |  |  | |  |  |  |  |  |  |  |  |  |  |  |  |
| Cohort data analysis |  |  | |  |  |  |  |  |  |  |  |  |  |  |  |
| Qualitative data analysis |  |  | |  |  |  |  |  |  |  |  |  |  |  |  |
| Cost data analysis |  |  | |  |  |  |  |  |  |  |  |  |  |  |  |
| Dissemination |  |  | |  |  |  |  |  |  |  |  |  |  |  |  |
| Academic Papers |  |  | |  |  |  |  |  |  |  |  |  |  |  |  |

## 5.3 Dissemination plan

Ongoing data from the cohort study will be shared with local, national and international stakeholders every 6 months in order to inform and improve the delivery of NCD care by MSF and other public health agencies in the study area. Outputs from the rest of the study such as the qualitative research will include briefing papers, reports and peer-reviewed academic publications and presentations at key conferences and workshops.

Specific outputs will include a briefing paper and overview report of all findings for MSF-OCA. Peer-reviewed academic publications will include a paper based on the each of the core methodologies, i.e. cohort analysis and qualitative data analysis, with additional papers focusing on relevant, identified mental health and NCD comorbidities and on implementation of the NCD guideline.

All team members will be authors on the journal publications; with author ordering based on time inputs in to the study and designated roles.

## 5.4 Financial resources

Routine data cleaning and will be covered by the MSF programme budget. All other costs relating to the study, including travel, transcription and translation of qualitative data, will be covered by the Manson Unit (MSF-OCA).

# 6 Limitations

The study design does not allow us to ascertain clinical impact or effectiveness of the programme since we have not included a comparator group. In addition, the two-year time frame and cohort size involved in this evaluation mean that typical clinical endpoints used in the study of chronic conditions, such as all-cause mortality, fatal and non-fatal myocardial infarction, cannot be measured. It is well established that improvement in surrogate measures i.e. clinical or biochemical parameters such as blood pressure, cholesterol or HbA1c, represents a reduction in cardiovascular risk^[[1]](#footnote-1)^. If maintained, this would result in a reduction in morbidity and mortality. In addition, improvements in clinical parameters are assumed to be due to the intervention itself but may be as a result of other, indeterminate factors, such as a patient receiving NCD care and/or medications from another source concurrently. Insight will be gained regarding this latter potential bias through focus groups and semi-structured interviews.

While literacy rates are quite high among Syrians (92% for men; 81 % women), we recognise this could still lead to potential bias in the adherence survey and also that literacy rates will vary by sub-group (e.g. based on gender, age, socio-economic background). To try and reduce this bias, a data collector will administer the adherence questionnaire to patients with limited literacy (and this will be recorded on the questionnaire).

In addition, this is a single-country case study focusing on a specific population (Syrian refugees and vulnerable Jordanians living in north Jordan), whose findings may not be generalizable to other settings and populations. However, the study addresses a major research gap and its findings are likely to inform actors with an interest in NCDs in humanitarian settings. The focus groups and interviews will be conducted by staff members from the implementing organisation (MSF) and are response-based, increasing the risk of social desirability bias. These risks will be mitigated by comprehensive explanation of the study to participants, with emphasis that participation will not influence the care they receive, and supervision by the principal investigator. Purposive sampling of interviewees may introduce selection bias. To minimise this bias, a broad sample of patients with a variety of demographic characteristics and medical conditions will be selected. Quantitative data are subject to measurement error and rigorous data cleaning will be undertaken.

# Annex 2: Data collection forms

## Annex 2a: Topic guide – Focus group discussions with NCD patients

| Key area | Themes | Question |
| --- | --- | --- |
| Introduction | Study aim and agencies involved | Why invited to participate? Consent & any questions? |
| Participant Background | Getting to know each other + building rapport | Could you tell us a bit about yourself? *Prompt: e.g. profession, what area live in, when you were first diagnosed with [NCD condition]?* |
| Reach | Access  Barriers to accessing care for NCDs  Ways of reducing barriers | What do you know about your NCD condition(s)? *Prompt – e.g. causes, types, who gets it, treatment*  Could you tell me about how you came to learn about your NCD condition(s)? ? *Prompt – e.g. from friends/family, from the radio (or other media), when diagnosed at hospital.*  What were you told about NCD condition(s) when you were enrolled in the MSF clinic? *Prompt – probe understanding of NCD condition(s) such as causes, risks and its management (medication and diet).*  What do you think might prevent people from attending this service for their NCD condition(s)? *Prompt: lack of knowledge, lack of services, costs, time, quality of services, stigma etc.*  How could access to healthcare for NCD condition(s) be improved? |
| Adoption and implementation | Information  Support | How did you feel when you were enrolled into this clinic? *Prompt: counselling/support experience. Prompt: subsequent days/weeks experience*  Who did you talk to about your experience at the clinic? *Prompt: E.g. family members, friends.*  What were you told about managing your NCD condition(s) after you were enrolled in clinic (by the NCD staff)? *Prompt: medicine types and usage, managing medicines, diet changes, risks and symptoms, frequency of check-ups etc.*  What sources of support did you receive in managing your NCD condition? *Prompt: emotional support from family/friends, information support from health workers, MHPSS from health workers.*  What made it easier for you to access care – initially and continuing care?  What made it difficult for you to access care – initially and continuing care?  What made it easier for you to self-manage your NCD condition at home?  What made it difficult for you to self-manage your NCD condition at home?  How acceptable do you find the NCD service / treatment. *Prompt: e.g. logistically, socially, culturally etc., differences with previous experience of treatment/ service?*  What has been your experience of the psychosocial services offered by the programme – group sessions/individual counselling*?* |
| Maintenance | Challenges  Supportive factors  To support adoption and implementation | What have been the main challenges in maintaining your medical treatment for your NCD condition? *Prompt: time, costs, information, drug supply, pill burden, stigma/shame etc.*  What have been the main challenges in altering your diet? *Prompt: information, costs, support*  What have been the main challenges in increasing your levels of exercise? *Prompt: information, suitable facilities or locations, physical condition, support, costs*  What have been the main challenges in reducing or quitting smoking? *Prompt: information, support, costs, desire*  What could have made accessing care easier for you? *Prompt: e.g. information given – content and way it was delivered; costs; type and quality of care and support; focus on role of the NCD programme/services.*  What could have made achieving lifestyle changes easier for you? *Prompt: e.g. information given – content and way it was delivered; costs; type and quality of care and support; focus on role of the NCD programme/services;*  What support is available to help you to continue to attend the clinic and self-manage your condition?  What additional supports regarding your NCD condition would you like to have? |
| Effectiveness | Unintended consequences  Benefits | What have been the negative consequences of taking NCD treatment / attending the service? *Prompt: physical, psych, costs, time.*  What have been the benefits of receiving NCD treatment / attending the service? *Prompt: e.g. physical, psychological, social, economic.*  What have been the benefits or negative consequences of attending group sessions/ individual counselling? |
| Thanks and  close | Anything else to add  Questions/Thanks, feedback info | Anything else to add on topic that we haven’t discussed today? Any questions for me? Feedback again on how the discussion will be used and fed back. |

## Annex 2b: Topic guide – Semi-structured interviews with NCD patients

The topic guides for the semi-structured interviews are indicative and they will be refined based on findings from the focus groups.

| Key area | Themes | Question |
| --- | --- | --- |
| Introduction | Study aim and agencies involved  Why invited to participate  Consent & any questions? |  |
| Participant Background | Getting to know each other + building rapport | Could you tell us a bit about yourself? *Prompt: e.g. profession, what area live in, when you were first diagnosed with NCD condition?* |
| Reach | Knowledge in community  Access to testing for [NCD condition]  Barriers to testing | What do you know about your condition? *Prompt – e.g. causes, types, who gets it, treatment*  What has been your experience in accessing healthcare and medications for your condition? *Prompt – in Syria, in Jordan, other NGOs or clinics, why choose to come to MSF clinic, does experience differ?*  Do you think a lot of people have your NCD condition in your community?  What do you think prevents people from accessing healthcare/medications for NCD conditions?  What do you think would make it easier for people to access healthcare / medications for NCD conditions?  If MSF were not providing this service what would you do to manage your condition? |
| Adoption and implementation | Information and other support provided  Adjusting to condition | What type of information provided to you about your condition and its treatment when you were enrolled in the MSF clinic? *Prompt: causes, who gets it, chronic nature, medicine types and usage, managing medicines, diet changes, risks and symptoms, frequency of check-ups etc.*  What sources of support did you receive? *Prompt: emotional support from family/friends, information support from health workers, psychosocial support from health workers*  What other support would you have liked to receive?  Do you find it easy to come in to the clinic from the beginning? *Prompt: facilitators or barriers e.g. logistically, socially, culturally*  How has having your NCD condition changed your daily life/routine? *Prompt: e.g. difficulties in changing your daily routine, in Syria or in Jordan?*  What is your experience of the MHPSS part of the programme (group sessions or individual counselling)? |
| Maintenance | Barriers/challenges to adhering to appointments and prescribed medicine/ lifestyle change. | Do you come in regularly for all your appointments? Do you find it easy or difficult to do so? Why? (e.g. travel, time, stigma)  What is your experience when you come to the clinic?  Do you experience any difficulties when you are visiting the clinic for follow up?  What could be done to make it easier for you to come to the clinic?  Do you take your medicines as often as you are prescribed? Why? *(Prompt: don't think it's important, unsure how to take them, can’t read the instructions, too many pills, share with family/ friends, supply rupture)* Do you find it easy or difficult to do so? Why? (*Prompt* *difficult to remember)*  Do you feel any pressure not to take your medicines (*Prompt: stigma from family or community, cost, medication sharing)*  What could be done to make it easier for you to take your medications?  Do you find it easy to maintain the recommended diet, exercise levels, smoking cessation for your condition?  What has helped you to make lifestyle changes? Prompt: health education, medical staff, family or community support?  What challenges do you face in adapting your diet, exercise levels and smoking habits?  Do you thing MHPSS is important?  What challenges do you face in taking part in or attending MHPSS support (group sessions, or individual counselling)? |
| Effectiveness | How coming to the clinic has affected patient's condition | What have been the negative consequences of taking treatment for the condition/ attending the service? *Prompt: physical, psych, costs, time.*  What have been the benefits of receiving treatment for your condition / attending the service? *Prompt: e.g. physical, psychological, social, economic.*  *What have been the positive and negative consequences for you in attending the MHPSS sessions (group or individual counselling)? (Prompt: feel supported, feel better, assists with managing NCD condition, upsetting, difficult)* |
| Thanks and  close | Anything else to add  Questions/Thanks, feedback info |  |

## Annex 2c: Topic guide – Semi-structured interviews with NCD health care providers and staff

The topic guides for the semi-structured interviews are indicative and they will be refined based on findings from the patient focus groups.

| Key area | Themes | Question |
| --- | --- | --- |
| Introduction | Study aim and agencies involved  Why invited to participate  Consent & any questions? |  |
| Participant Background | Getting to know each other + building rapport | Could you tell us a bit about yourself? Prompt: e.g. professional, involvement in the NCD service at Irbid (and previously if relevant)? |
| Reach | Access  Barriers to NCD care provision  Ways of reducing barriers | What are the key challenges for patients to access healthcare (medications, regular clinical review, investigations, interventions) for their NCD condition(s) e.g. knowledge, costs, time, availability or quality of care [expand], stigma etc.  How could access to healthcare for NCD condition be improved? Prompt: improve knowledge (e.g. outreach, radio, health workers etc.), improve availability of services, quality of services etc. |
| Adoption and implementation | Information and support | What types of information are provided to patients when they are enrolled in/ attend the NCD service?  What sources of support are offered to patients when they are enrolled in/ attend the NCD service)?  How acceptable do you think the MSF NCD programme, including treatment, is for patients? Prompt: e.g. quality, responsiveness, socially, culturally etc.  What is your experience with implementing the new MSF NCD guideline?  What sources of support and information were available to you to facilitate implementing the guideline? |
| Maintenance | Challenges  Supportive factors  To support adoption and implementation | What do you think are the main challenges facing NCD patients here in terms of managing their condition? Prompt: medicines/testing/attendance - time, costs, information, drug supply etc.; lifestyle changes – knowledge, social/cultural pressures etc.  What could be done to make it easier for NCD patients to access care? Prompt: e.g. information given – content and way it was delivered; costs; type and quality of care and support; [note: focus on role of the [NCD condition] programme/services].  What do you think are the main challenges facing staff here in terms of delivering the NCD care programme in Irbid? Prompt: time, training, clinical support/supervision, guidelines or tools  What could be done to make it easier for staff to deliver this NCD care programme? Prompt: knowledge, time, training, clinical support/supervision, guidelines or tools  What are the benefits of using the MSF NCD guideline?  What are the challenges around using the MSF NCD guideline?  What could be done to facilitate implementation of the guideline? |
| Effectiveness | Unintended consequences  Benefits | What are the benefits of the NCD care programme in Irbid? Prompt: more efficient, less complications, for patients, for staff, for system, for community etc.  What are negative consequences of the NCD care programme in Irbid? Prompt: time, complexity, costs etc. for patients, for staff, for system, for community  What particular aspects of the programme have helped or hindered NCD care? Prompt: clinical aspects, task shifting, introduction of HLO, MHPSS, HV, structures, tools, systems  What particular aspects of the guideline have helped or hindered NCD care? Prompt: supports decision making, ease of use, contradictory, not acceptable to patients, different to usual practice in Jordan. |
| Thanks and  close | Anything else to add  Questions  Thanks, feedback info | Anything else to add on topic that we haven’t discussed today?  Any questions for me?  Feedback again on how the discussion will be used and fed back. |

##

## Annex 2d: Topic guide – Semi-structured interviews with key stakeholders

The topic guides for the semi-structured interviews with key stakeholders are indicative and they will be refined based on findings from the patient focus groups and interviews and will vary depending on respondent type.

| Key area | Themes | Question |
| --- | --- | --- |
| Introduction | Study aim and agencies involved  Why invited to participate  Consent & any questions? |  |
| Participant Background | Getting to know each other + building rapport | Could you tell us a bit about yourself? Prompt: e.g. professional, involvement in the NCD service at Irbid (and previously if relevant)? |
| Reach | Access  Barriers to NCD care provision  Ways of reducing barriers | What are the key challenges for patients to access healthcare (medications, regular clinical review, investigations, interventions) for their NCD condition(s) e.g. knowledge, costs, time, availability or quality of care [expand], stigma etc.  How could access to healthcare for NCD condition be improved? Prompt: improve knowledge (e.g. outreach, radio, health workers etc.), improve availability of services, quality of services etc. |
| Adoption and implementation | Information and support | How acceptable do you think the MSF NCD programme, including treatment, is for patients? Prompt: e.g. quality, responsiveness, socially, culturally etc. |
| Maintenance | Challenges  Supportive factors  To support adoption and implementation | What do you think are the main challenges facing NCD patients in this area in terms of managing their condition? Prompt: medicines/testing/attendance - time, costs, information, drug supply etc.; lifestyle changes – knowledge, social/cultural pressures etc.  What could be done to make it easier for NCD patients to access care? Prompt: e.g. information given – content and way it was delivered; costs; type and quality of care and support; [note: focus on role of the [NCD condition] programme/services].  What do you think are the main challenges facing staff here in terms of delivering the NCD care programme in Irbid? Prompt: time, training, clinical support/supervision, guidelines or tools  What could be done to make it easier for staff to deliver NCD care programme? Prompt: knowledge, time, training, clinical support/supervision, guidelines or tools  What are the benefits of using the MSF NCD guideline? [ask if appropriate]  What are the challenges around using the MSF NCD guideline? [ask if appropriate]  What could be done to facilitate implementation of the guideline? [ask if appropriate] |
| Effectiveness | Unintended consequences  Benefits | What are the benefits of the NCD care programme in Irbid? Prompt: more efficient, less complications, for patients, for staff, for system, for community etc.  What are negative consequences of the NCD care programme in Irbid? Prompt: time, complexity, costs etc. for patients, for staff, for system, for community  What particular aspects of the programme have helped or hindered NCD care? Prompt: clinical aspects, task shifting, introduction of HLO, MHPSS, HV, structures, tools, systems  What particular aspects of the guideline have helped or hindered NCD care? Prompt: supports decision making, ease of use, contradictory, not acceptable to patients, different to usual practice in Jordan. |
| Thanks and  close | Anything else to add  Questions  Thanks, feedback info | Anything else to add on topic that we haven’t discussed today?  Any questions for me?  Feedback again on how the discussion will be used and fed back. |

## Annex 2e: Clinical audit sample checklist

|  | Condition | YES | NO | N/A |
| --- | --- | --- | --- | --- |
| 1.0 | Diabetes | | | |
| 1.1 | Micro-albuminuria or urinary protein tested in the last year (Target = 80%)  ? | Y | N | N/A |
| 1.2 | Correct action taken based on micro-albuminuria test result? (Target = 80%)  ? | Y | N | N/A |
| 1.3 | Baseline CVD risk score done on enrolment? | Y | N | N/A |
| 1.4 | Prescribed statin in accordance with guideline (if risk score > 20% or known CVD)? |  |  | N/A |
| 1.5 | On ACE inhibitor (ACEi) inhibitor for HTN if no contraindication (Target 80%)  ? | Y | N | N/A |
| 1.6 | Creatinine tested prior to ACEi initiation? (Target 80%) | Y | N | N/A |
| 1.7 | Annual foot check done? (Target 80%) | Y | N | N/A |
| 1.8 | Correct foot score calculated? (Target 80%) | Y | N | N/A |
| 1.9 | Correct action taken based on foot score? (Target 80%) | Y | N | N/A |
| 1.10 | Annual eye check done or referral made? (Target 80%) | Y | N | N/A |
| 2.0 | Hypertension | | | |
| 2.1 | Annual glucose check done if not known diabetic? (Target 80%) | Y | N | N/A |
| 2.2 | Correct action taken if above target (diagnose diabetes or perform second test as per guideline)? (Target 80%) | Y | N | N/A |
| 2.3 | Annual CVD risk score done? (Target 80%) | Y | N | N/A |
| 2.4 | Annual cholesterol checked if not prescribed a statin? (Target 80%) | Y | N | N/A |
| 3.0 | Asthma | | | |
| 3.1 | Annual control review done (Target = 80%) | Y | N | N/A |
| 3.2 | Action taken following control review as per guideline i.e. step down/up on medications as appropriate? (T 80%) | Y | N | N/A |
| 3.3 | Inhaler technique check documented? (Target 80%) | Y | N | N/A |
| 4.0 | Referral | | | |
| 4.1 | Referral to acute care/specialist service appropriate according to guideline? (T 80%) | Y | N | N/A |

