1. Patients who have an NCD other than those named above are not admitted to the programme but are referred to the MoH or other service providers where available e.g. isolated hypothyroidism is referred to the International Rescue Committee clinic.

2. Co-morbid NCDs in addition to those named above, which may be treated at primary care level with medications included in the MSF Essential Drug List, are managed within the programme e.g. providing analgesia for osteoarthritis pain or anti-acid medications for gastritis.

3. NCDs that are not managed by the programme currently e.g. cancer, or complications of the named NCDs requiring secondary or tertiary care input, are referred to MoH services or to other NGOs where available e.g. retinal screening for diabetic patients is provided by the Qatari Red Crescent hospital in Irbid.

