**Table 1. Standard epidemiological and quality indicators for MSF NCD services**

### 1.1.4 Evolution of model of care

| **Epidemiological / service activity indicators** | **Quality indicators** |
| --- | --- |
| Number / % of new patient consultations per month | Number / % of DM patients that have micro-albuminuria or urinary protein testing in the last year (Target = 80%) |
| Number / % of follow-up consultations per month (% of total visits) (by age, gender, nationality) | Number / % of patients with DM or on ACE inhibitor (ACEi) with Creatinine testing in last year (Target 80%) |
| Number/ % of patients presenting with the following morbidities: DM Type I, DM Type II, Hypertension,  other CVD, Asthma, COPD, Hypothyroidism, other | Number/ % asthma and COPD patients who receive control review (spirometry or clinical) in last year (Target = 80%) |
| Number of new diagnoses over a period of time | Number/% of asthmatics with acute exacerbations/ admissions in last year (Target = 20%) |
| Number/ % of exits per month: % defaulter, % dead (by primary diagnosis),  % self-transferred, % other | Number / % of DM patients/ hypertensives with mean BP <= 140/90 over last 12 months  (Target = 80%) |
|  | Number / % of DM patients with mean HbA1C < 8.0 % (or average FPG<150) in last 12  months (Target = 80%) |

Programmatic changes over time include introduction of: (1) a home visit team (2) a humanitarian liaison officer and (3) a formal MHPSS service. Technical changes introduced over time include: (1) task shifting to nurses of follow-up consultations (2) introduction of MSF-OCA NCD Guidelines and (3) implementation of spirometry. Contextual changes that occurred since programme inception include: (1) introduction of co- payments by the Jordanian government for Syrian refugees accessing MoH primary care services in November 2014 (2) increased recruitment of vulnerable Jordanians to the MSF NCD programme in the last quarter of 2015 and (3) closure of the MSF NCD programme to new patients from May to October 2016.

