| Implementation  To what extent was the intervention delivered as intended?  What are the facilitators and barriers to implementing the programme from a patient, provider and programmatic perspective?  What are the essential components and adaptations necessary to delivering an NCD service in this setting?  What are the start-up and incremental costs of delivering such a service? | Fidelity of programme delivery  (Process Indicators;  indicators in bold also reflect quality of medical care) | Extent to which clinical guideline delivered as intended:  Number / % of eligible patients with HTN with annual FPG performed during the reporting period  Number/ % of eligible patients with diabetes that have had an annual foot check/ eye check performed during the reporting period  Number / % of DM patients that have micro-albuminuria or urinary protein testing during the reporting period  Number / % of DM patients on ACE inhibitor (ACEi) with Creatinine testing during the reporting period  Number/ % asthmatics and COPD with control review (spirometry or clinical) during the reporting period  Number / % of active cohort attending a health education session at last clinical visit within reporting period  Number of MHPSS group sessions taking place monthly during reporting period  Number/ % of referred patients attending MHPSS individual counselling sessions  Number/ % of times when clinical action taken based on clinical or laboratory findings according to guideline (see Annexe 2d for detail) | Clinical audit  Participant observation  Routine health facility cohort data |
|  | Adaptations | NCD care adaptations to the local setting (e.g. cultural adaptations; dietary and exercise, smoking advice)  Programme adaptations related to humanitarian setting and role e.g. response to patients’ psychosocial needs and NCD-relevant mental health co-morbidities | Key informant interviews  Participant observation  Semi-structured interviews with 12 MSF/clinic staff and 16 patients |
|  | Cost | Staff time  Start-up and recurrent implementation costs (indirect, intermediate and final cost centres)  Average unit costs and unit costs stratified by morbidity) | Key informant interviews  2 Focus groups with  Medicine/supply/ staff costs  Staff time estimates |

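### Audit item 1.10 merges eye checks done with eye referrals made, so it would overstate the Table 2 eye-check indicator by the referrals not completed

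*Protocol*

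**What the plan says.** **Eye check.** Table 2, under fidelity of programme delivery, defines the indicator as "Number/ % of eligible patients with diabetes that have had an annual foot check/ eye check performed during the reporting period". The sources for that row are given together as "Clinical audit Participant observation Routine health facility cohort data", with no source assigned to each indicator. In Annex 2e, item 1.10 reads "Annual eye check done or referral made? (Target 80"%), with a single Yes, No or N/A. The foot check shares the same Table 2 line, but its item 1.7 has no referral alternative: "Annual foot check done? (Target 80"%).

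**Where eye screening happens.** Section 1.1.1 states that "retinal screening for diabetic patients is provided by the Qatari Red Crescent hospital in Irbid". Referral and examination are therefore separate events at separate places.

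**Creatinine.** Table 2 asks for "Number / % of DM patients on ACE inhibitor (ACEi) with Creatinine testing during the reporting period". Table 1, the programme's standard indicators, has "Number / % of patients with DM or on ACE inhibitor (ACEi) with Creatinine testing in last year (Target 80"%). The only creatinine item on the checklist is 1.6: "Creatinine tested prior to ACEi initiation? (Target 80"%).

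**The concern.** The eye item and the eye indicator count different events, and a single tick-box cannot be separated afterwards without reopening the files. If the audit supplies the indicator, referrals that led to no examination enter the numerator as checks performed.

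The routine data may not repair this. Section 1.1.6 lists recommended specialist referrals and laboratory results among the data routinely recorded, but no eye examination. On that list, routine data could show the referral but not the check. The audit is then the file-level source best placed to show whether the check took place, and its form discards that information.

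At stake is one fidelity indicator, not a principal outcome of section 3.4.2. It would still be a misleading figure in an evaluation meant to show how far the guideline was delivered.

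**Working it through.** The protocol states no rate for either indicator, so there is no figure to reproduce. The check compares definitions and then illustrates size with assumed values.

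**Eye check: who is scored how**

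- Examined in the reporting period: Yes on item 1.10, counted in Table 2.
- Referred, not examined: Yes on item 1.10, not counted in Table 2.
- Neither: No on item 1.10, not counted in Table 2.

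Only the middle group is discordant, and always in the same direction.

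**Eye check: size**

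Let p be the share of eligible diabetic patients examined, and r the share of the remainder who were referred. Then:

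- item 1.10 rate = p + (1 − p) × r
- Table 2 indicator = p
- overstatement = (1 − p) × r, which is zero or positive

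Both p and r are assumptions. These pairs all bring item 1.10 to 80%:

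| p (Table 2) | r | (1 − p) × r | Item 1.10 |
|---|---|---|---|
| 30% | 71.4% | 50 points | 80% |
| 50% | 60% | 30 points | 80% |
| 60% | 50% | 20 points | 80% |
| 70% | 33.3% | 10 points | 80% |

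A reading of 80% on item 1.10 is thus compatible with very different values of the indicator. The formula takes it that every check performed is found in the file or preceded by a recorded referral.

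**Creatinine: same comparison**

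Let a be the share tested before starting the ACE inhibitor and b the share tested in the reporting period. Both are assumed, and taken as independent for illustration.

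- a = 80%, b = 70%: passes 1.6 but fails Table 2 = 0.80 × 0.30 = 24%; fails 1.6 but passes Table 2 = 0.20 × 0.70 = 14%. Item 1.6 is 10 points too high.
- a = 70%, b = 80%: 0.70 × 0.20 = 14% and 0.30 × 0.80 = 24%. Item 1.6 is 10 points too low.

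Over a = 70–90% and b = 50–80%, the first group runs from 14% to 45% and the second from 5% to 24%. The two measures differ, but not in a fixed direction.

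**The case against.** **The eye wording has a rationale.** The row is about delivering the guideline as intended. With screening done elsewhere, referral is the step that the clinics control. This is a fair reason to record referrals. It does not make a referral a check performed, which is what Table 2 counts, and recommended referrals already have their own checklist item (4.1) and Table 2 indicator.

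**A reader might infer that the programme could appear to meet an eye target that it misses.** The protocol does not support this. Table 2 sets no targets, Table 1 has no eye indicator, and the only 80% eye target is attached to the combined wording of item 1.10. A programme at 80% on that item meets the target as written. What fails is the use of that figure for the Table 2 indicator.

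**A reader might infer that item 1.6 replaces the Table 2 creatinine indicator and flatters it.** This is not supported either. Nothing links item 1.6 to that indicator. Kidney function tests are done at the first visit and repeated annually (section 1.1.2), laboratory results are recorded routinely (section 1.1.6), and routine cohort data are a listed source for the row. The difference can also go either way. Whether a patient tested once before starting in early 2015 fails Table 2 depends on the reporting period, which is not defined: if it spans January 2015 to December 2016, that patient may pass.

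**The annex is titled a sample checklist.** This stands. It lowers the weight of the point and means that the form can still be changed.

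**Conclusion.** The eye-check mismatch stands. Item 1.10, reported as the Table 2 eye indicator, overstates it by the share of eligible diabetic patients who were referred but not examined. The protocol gives no referral completion rate, so the size is unknown; the 10 to 50 points in the table are illustrations only. The conclusion rests on the audit being used for this indicator, as Table 2 allows, and on checks performed being visible in the file or preceded by a recorded referral.

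The creatinine point is secondary. Item 1.6 measures something other than the Table 2 creatinine indicator, without a fixed direction of error, and matters only if it is reported against that indicator. Neither point says anything about when patients should be tested or referred.

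**What to change.** Before the audit starts:

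1. Split item 1.10 into (a) eye check performed in the reporting period and documented in the file, and (b) referral made, no check documented. Use the Table 2 time window for (a), and write down what the reporting period is.
2. Report (a) alone against the Table 2 indicator, and (a) plus (b) against the checklist's own 80% target. State which of the two the target refers to.
3. Show the two figures side by side as lower and upper bounds. The upper bound holds if every undocumented outside check followed a recorded referral.
4. For creatinine, state that the Table 2 indicator comes from routine laboratory data, or add a checklist item with the Table 2 time window. Keep item 1.6 as a separate item and do not report it against that indicator.

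The cost is one or two extra tick-boxes on the same files with the same staff. The downside is that the rate reported against Table 2 will be lower if any referrals went uncompleted, and outside checks that never reached the file will be missed. That is why both figures should be shown.
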